##### Reporting of serious adverse events

All fatal and life-threatening SAEs occurring after study drug initiation and up to the end of study visit must be reported on AE pages in the CRF and on an SAE form, regardless of the investigator-attributed causal relationship with study treatment.

No other SAEs are required to be reported on AE page of the CRF and on the SAE form to Sobi drug safety department.

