## 4 Investigational plan

### 4.1 Overall study design and plan

This is a randomized, open-label, parallel group, 2-arm multicenter study to investigate the efficacy and safety of anakinra in reducing hyper-inflammation and respiratory distress in adult patients with severe COVID-19 and CSS pneumonia.

The study consists of screening, a 2-week treatment period and a 2-week follow-up period.

The 2-week treatment period is open, and the patients will be randomized to treatment with anakinra + standard of care or standard of care alone in a 1:1 ratio.

Anakinra will be administered as 4-times daily i.v. infusions for a maximum of 15 days (Days 1 to 15), according to the patient health status and expert clinical opinion. The primary endpoint will be evaluated at Day 15.

According to hospital internal protocol, if the patient improves enough to recommend his/her discharge before the 15th day of the study, the patient will be able to continue receiving the medication at home by s.c. administration (100mg/6 hours). In any case, follow-up visits by telephone or in person will be made, depending on where the patient is, until the end of the study.

The study duration for an individual patient will not exceed 4 weeks. The end of the study is defined as last patient last follow-up visit/phone call.

Figure 1:

[figure not shown]

The study design has a total sample size of 180 patients and consists of two stages. At the end of the treatment stage, the success rates are compared between each arm: anakinra + standard of care treatment vs standard of care alone.

A data review committee composed of experts in internal medicine will be involved in the study oversight and interpretation of the study results.

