| MEWS score                                     |   | X   |   |   | X |   |
| Survival                                       |   |     |   |   |   | X |
| Time to hospital discharge                     |   |     |   |   |   | X |
| Adverse events                                 |   | X   | X | X | X |   |
| Biomarkers                                     |   | X   | X | X | X |   |

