#### *4.5.1.6 Follow-up (Day 28)*

These visits can be conducted either as a follow-up telephone call or in-person visit, if the patients is still hospitalized. Please refer to Table 3 for the clinical parameters to be collected during the visits.

A window of  $\pm 5$  days will be allowed.

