#### 4.5.3.4 Oxygen supplementation

Oxygen supplementation will be assessed at Visits 1 to 5. The date, time and amount of supplementation will be recorded in the CRF.

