#### 4.5.3.7 Survival and hospital discharge

Data on survival and hospital discharge will be collected at Visits 5 and 6 and recorded in the CRF.

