##### Follow-up of serious adverse events

Serious adverse events still ongoing at the end of study visit must be followed up until resolution or stabilization, or until the event outcome is provided, e.g., death.

---

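### Life-threatening SAEs are reportable up to the end-of-study visit, but Table 3 schedules no adverse-event enquiry after Visit 4 (Day 15), so non-fatal ones in follow-up rest on spontaneous reporting

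*Protocol*

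**What the plan says.** Two parts of the protocol bear on how long serious events are collected.

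**The reporting rules (section 4.5.4.3).** On serious events: "All fatal and life-threatening SAEs occurring after study drug initiation and up to the end of study visit must be reported on AE pages", and on an SAE form as well. On follow-up: "Serious adverse events still ongoing at the end of study visit must be followed up until resolution or stabilization". Section 4.1 fixes the end point: "The end of the study is defined as last patient last follow-up visit/phone call". For the individual patient, the last contact in Table 3 is Visit 5/TC, Day 28.

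**The schedule (sections 4.5.1.1 and 4.5.1.6).** The adverse-event row of Table 3 carries marks at Visits 1, 2, 3 and 4 (Days 1, 4, 7 and 15) and none at Visit 5/TC. The text for the Day 28 contact adds no question of its own and defers to the table: "Please refer to Table 3 for the clinical parameters to be collected during the visits". The rows that are marked at Visit 5/TC are oxygen supplementation, survival and time to hospital discharge.

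**The concern.** The reporting rule and the data-collection schedule stop at different times. The rule covers fatal and life-threatening SAEs up to the final contact, whereas the schedule stops asking about adverse events at Day 15. A site that follows section 4.5.1.6 exactly would telephone a discharged patient on Day 28, record whether the patient is alive, when discharge took place and whether oxygen is in use, and end the call without asking about serious events since Visit 4.

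The event class exposed is the non-fatal life-threatening SAE. Section 3.2.1 lists treatment-emergent fatal and life-threatening SAEs among the secondary endpoints, and section 6.3.4.4 tabulates adverse events by treatment. If capture after Day 15 depends on whether the site happens to be told, it will tend to be better for patients still in hospital than for those at home. The trial is also open-label, so unsolicited reporting could differ by arm. An analysis plan cannot repair this, because it cannot recover events that nobody asked about.

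**Working it through.** There is no stated figure to reproduce. The check sets the sections side by side and then counts days.

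**Step 1. Is the blank cell real, or a fault of table extraction?** The oxygen row has a mark in the Visit 5 column, and section 4.5.3.4 confirms it independently: "Oxygen supplementation will be assessed at Visits 1 to 5". Survival and time to discharge are also marked there, and section 4.5.3.7 agrees as to Visit 5: "Data on survival and hospital discharge will be collected at Visits 5 and 6 and recorded in the CRF". The columns therefore line up, and the adverse-event row is blank at Visit 5/TC.

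**Step 2. Does any other section add a Day 28 enquiry?**

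| Item | Section | Last scheduled time |
|---|---|---|
| Adverse events | 4.5.1.1, Table 3 | Visit 4 (Day 15) |
| Requirement for mechanical ventilation | 4.5.3.1 | Visit 4 |
| Laboratory assessments | 4.5.3.6 | Visit 4 |
| Vital signs | 4.5.4.7 | Day 15 |
| ECG | 4.5.4.8 | Day 15 |
| Oxygen supplementation | 4.5.3.4 | Visit 5 (Day 28) |
| Survival, hospital discharge | 4.5.3.7 | Visit 5 (a Visit 6 is also named, which Table 3 lacks) |

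No section adds one. The continuous safety review in sections 4.5.4.5 and 4.5.4.11 works on what sites have collected and does not itself question patients.

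**Step 3. Which reportable events are left without a scheduled enquiry?** The rule names two classes.

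- Fatal SAEs: covered, because survival is collected at Day 28.
- Non-fatal life-threatening SAEs: not covered by any item marked at Visit 5/TC.

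**Step 4. How long is the stretch?**

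- Nominal: Days 16 to 28 = 28 − 15 = 13 days, and 13/28 = 46% of the 28 days.
- With the Table 3 windows, Visit 4 falls on Days 13 to 17 and Visit 5 on Days 26 to 30. Shortest interval 26 − 17 = 9 days; longest 30 − 13 = 17 days.
- With the ±5 days that section 4.5.1.6 gives for the Day 28 contact, Visit 5 falls on Days 23 to 33. Shortest interval 23 − 17 = 6 days; longest 33 − 13 = 20 days.

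The Day 28 window differs between Table 3 (±2) and section 4.5.1.6 (±5), which is a separate inconsistency. The conclusion is the same under either.

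**The case against.** The strongest reply is that the duty to report depends on events, not on visits. Section 4.5.4.3 requires fatal and life-threatening SAEs to be reported within 24 hours of the investigator's first knowledge, whatever treatment was received, and makes the investigator responsible for obtaining the information when a patient is admitted to another hospital. A blank table cell cancels none of that, and a Day 28 conversation about survival, discharge and oxygen may well bring a serious event to light. This stands, and it limits the point: the gap is in scheduled ascertainment, not in the duty to report. It does not remove the gap, because the 24-hour clock starts only once the site knows, and nothing scheduled ensures that it finds out.

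A reader might infer more than the protocol supports:

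- *That no events after Day 15 are sought.* Deaths are, through the survival item.
- *That special-interest events are caught in the same contradiction.* Section 4.5.4.3 gives them no end date, so the end-of-study rule does not reach them. Dosing ends by Day 15 at the latest, so an event leading to discontinuation cannot first arise afterwards, and the stated half-life of 4 to 6 hours makes late drug-related anaphylaxis unlikely.
- *That a planned Day 28 safety comparison is spoiled.* None is specified. Section 4.1 speaks only of a follow-up period, and section 6.3.4.4 gives incidence tables without a Day 28 analysis.
- *That the last neutrophil count is mistimed, because Visit 4 may fall on Day 13 while dosing may run to Day 15.* This contradicts nothing in the protocol; it follows from an ordinary visit window, and changing it would mean a new monitoring rule.

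**Conclusion.** The mismatch is real but narrow. The reporting and follow-up rules in section 4.5.4.3 need SAE status up to the final contact, while Table 3, and section 4.5.1.6 through it, schedule no adverse-event enquiry there. Non-fatal life-threatening SAEs between Visit 4 and Visit 5 therefore rest on spontaneous reporting.

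The 46% measures calendar time without a scheduled enquiry and should not be read as a share of events missed, since the protocol gives no event rate. Nor is it the whole post-treatment period for every patient: dosing lasts at most 15 days, and someone who stops early has scheduled checks after the last dose. How far the listed SAE endpoint suffers is also open, because it is restricted to treatment-emergent events and the protocol does not say how long after the last dose an event still counts.

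That capture would be poorer in discharged patients, and might differ by arm in an open-label trial, is a reasonable expectation and not something the protocol demonstrates. The conclusion assumes that sites follow the schedule as written. The Day 15 primary endpoint and mortality are unaffected. The point should be corrected because the remedy is almost free.

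**What to change.** Reconcile the schedule with the reporting rules in two places:

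1. In Table 3, mark the adverse-event row at Visit 5/TC, for both arms.
2. In section 4.5.1.6, add a sentence that the Day 28 call or visit asks about fatal and life-threatening SAEs since Visit 4.

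The cost is one table mark, one sentence and a few added questions in a contact that already takes place. No extra visit or sample is needed. The same edit could settle the Day 28 window (±2 or ±5 days) and the reference to a Visit 6 in section 4.5.3.7, so that all sections describe the same final contact.

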##### Abnormal laboratory findings

Abnormal laboratory findings, if serious (fatal or life-threatening), must be reported on specific AE pages of the CRF.

Following laboratory variables are collected for the assessment of efficacy (see Section 6.5.3.2) at screening and during the treatment period, and are not required to be reported as SAEs as described above: WBC including differential counts, RBC, Hgb, platelet count, fibrinogen, PT-INR, and cardiac troponin; ALT, AST, total bilirubin, creatinine, ferritin, LDH, D-dimer, and CRP.

##### Follow-up of serious adverse events

Serious adverse events still ongoing at the end of study visit must be followed up until resolution or stabilization, or until the event outcome is provided, e.g., death.

---

### Reporting procedures

All fatal and life-threatening SAEs must be reported by the investigator to the Sobi drug safety department within 24 hours of the investigator's first knowledge of the event.

All fatal and life-threatening SAEs must be recorded on an SAE form, irrespective of the study treatment received by the patient, and whether or not this event is considered by the investigator to be related to study treatment.

The SAE forms must be e-mailed to the Sobi drug safety department: [[contact]](mailto:[contact]).  
In copy: [[contact]](mailto:[contact]).

The investigator must complete the SAE form in English and must assess the causal relationship of the event to study treatment.

Follow-up information about a previously reported SAE must also be reported within 24 hours of receiving it. The Sobi drug safety department may contact the investigator to obtain further information.

If the patient is hospitalized in a hospital other than the study site, it is the investigator's responsibility to contact this hospital to obtain all SAE relevant information and documentation.

The reference safety document to assess expectedness of a suspected serious adverse reaction and for reporting by the Sponsor to Health Authorities, IRBs/IECs, and investigators is: Section 4.5.4.3.

#### *4.5.4.4 Pregnancy*

### Reporting of pregnancy

Irrespective of the treatment received by the patient, any pregnancy occurring after study drug initiation up to the end of study visit must be reported within 24 hours of the investigator's knowledge of the event.

Pregnancies must be reported on the pregnancy form which is e-mailed to the Sobi drug safety department ([[contact]](mailto:[contact]) and [[contact]](mailto:[contact]), in copy), and on an AE page in the CRF.

---

### Follow-up of pregnancy

Any pregnancy must be followed to its conclusion and its outcome must be reported to the Sobi drug safety department. This information will be only entered in the drug safety database.

Any AE associated with the pregnancy occurring during the study must be reported on separate AE pages in the CRF. Any SAE occurring during the pregnancy must be reported on an SAE form as described in Section 4.5.4.3.

#### *4.5.4.5 Study safety monitoring*

Clinical study safety information is monitored and reviewed on a continuous basis by the Sobi Pharmacovigilance Team (in charge of ensuring patients' safety as well as data quality).

#### *4.5.4.6 Laboratory safety assessments*

For details on laboratory assessments, see Table 3.

#### *4.5.4.7 Vital signs*

Vital signs (body temperature, blood pressure, heart rate, respiratory rate and oxygen saturation) will be measured at screening, and Days 1, 4, 7 and 15, and recorded in the CRF.

For AE reporting of abnormalities, see Section 4.5.4.3.

#### *4.5.4.8 Electrocardiograms*

A 12-lead ECG recording will be performed at screening and at Day 15 and recorded in the CRF. The ECG assessments will be performed at site and will be reported as “normal” or “abnormal”. Any abnormalities should be specified. Abnormalities reported at screening should be recorded as medical history.

For AE reporting of abnormalities, see Section 4.5.4.3.

#### *4.5.4.9 Pregnancy Test*

Pregnancy is not recommended during the study. Sexual abstinence and the use of contraceptives will be recommended.

Female of childbearing potential will have a urine pregnancy test taken at screening and at Day 15. The outcome of the test will be reported as “positive” or “negative” in the CRF.

---

#### *4.5.4.10 Data Review Committee*

The Data Review Committee composed of experts in internal medicine will be involved in study oversight and interpretation of the study results.

#### *4.5.4.11 Safety Review Committee*

Clinical safety information (AEs, SAEs, laboratory values, ECGs, vital signs, and study-specific labs/examinations, as required) will be monitored and reviewed on a continuous basis by the Clinical Review Committee (CRC) by periodically monitoring clinical studies activities from protocol conception to database closure. There will be separate written operating procedures for the CRC.

#### *4.5.5 Exploratory assessments*

Blood samples for determination of IL-6 and selected exploratory parameters will be collected at Day 1, 7 and 15, whenever possible. The date and time of sampling will be recorded in the CRF.

All samples will be analyzed at the respective hospital local laboratory according to their standard routines.

---

## 5 Quality control and quality assurance

This study will be conducted in compliance with this protocol, and applicable regulatory requirements.

The Sponsor will establish a systematic, prioritized, risk-based approach to monitoring and, considering the current situation, will need to utilize remote monitoring. The Sponsor will develop a risk management plan with the aim to limit the contacts with patients and site personnel during the emergency period, while ensuring the patients safety and integrity, compliance with the protocol, study specific procedures and applicable regulatory requirements.

To ensure ongoing patient safety and well-being, and control risks to study critical processes, such as review of all informed consent forms and all primary efficacy variables, alternative mechanisms of oversight will be introduced (such as phone calls, video calls etc).

All information must be transcribed from clinical history to the study CRF. In this study a paper CRF will be used to capture all study data.

The study site may be subject to a quality assurance audit by the Sponsor or its representatives, as well as inspection by appropriate regulatory agencies.

It is important that the investigator(s) and the(ir) relevant personnel are available during the monitoring visits and possible audits and that sufficient time is devoted to the process.

## 6 Statistical plan

### 6.1 Determination of sample size

The study will enroll a total of 180 patients, 90 per arm according to the 1:1 randomization. The sample size has been estimated based on the following assumptions:

- The sample size is calculated in based of the data collected in the database of COVID-19 of the Complejo Hospitalario de Navarra , which currently has a total of 188 patients. After the analysis of the data, it is estimated that 15% of severe pneumonia COVID patients have required mechanical ventilation.
- For and Type I error of 0.05 and a power of 75% for each comparison under the assumption that the true success rates are 88% in the SoC group increasing to 92% in the anakinra group.
- It is needed 180 patients (90 per arm) considering a loss of 10%.
- The study will consist of two stages, with equal numbers of patients randomised into Stage 1 (treatment) and into Stage 2 (follow-up) per treatment arm.

The calculations on the operating characteristics of this design have been undertaken using the website of Sample size calculator of *National Center for Advancing Translational Sciences, National Institutes of Health*, through [UCSF-CTSI](#) , Software utilities developed by [[contact]](mailto:[contact]), last up to date version on April 14, 2020.

The value for the type I error has been chosen in recognition of the urgent unmet medical need to allow the identification of a signal, at least, from a statistical perspective. Having seen a statistical signal, it is then a matter of evaluating whether the observed treatment differences represent clinically relevant effects that can satisfy that unmet need.

In case indications of efficacy requires to be confirmed, additional patients may be added into this study.

In case the outcome is statistically convincing, efficacy will be considered confirmed and the results will, where warranted, be used to seek regulatory approvals.

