### 2.3 Potential risks and benefits

The potential applicability of the results of this clinical trial, in an extraordinary health emergency such as COVID-19, is obvious. Positive results could help to define the standard treatment of severe COVID-19 pneumonia and have a dramatic impact on both local and global morbidity and mortality. Negative results would constitute very useful scientific evidence for abandoning unfounded empirical approaches and would help redirect resources and efforts in another more promising direction. The expected length of time needed for recruitment is 3-4 weeks, depending on the epidemiological progression of the pandemic in our centers, so results could be available in early May 2020.

Anakinra is a recombinant form of the human IL-1Ra, r-metHuIL-1Ra, which is produced by recombinant DNA technology in an *E. coli* expression system. Therapeutically, anakinra neutralizes the biological activity of IL-1 (IL-1 $\alpha$  and IL-1 $\beta$ ) by competitively inhibiting its binding to the IL-1RI.

Kineret (anakinra) was first approved for treatment of RA in the US in 2001 and subsequently in the EU/EEA in 2002. In 2012, an sBLA on anakinra for treatment of NOMID was approved in the US. Kineret is also approved for treatment of CAPS (in EU/EEA, Israel and Australia), Still's disease, including SJIA and AOSD (in EU/EEA) and SJIA (in Australia).

The initial IND for anakinra was granted in 1991. The estimated cumulative exposure to anakinra in completed company sponsored clinical studies up to 1 May 2018 is 6404 subject-years, in 8518 subjects with various indications. Anakinra is administered s.c. at doses of 100 mg/day (RA) or in weight-based doses of up to 8 mg/kg/day (NOMID). In clinical studies in sepsis, doses up to 2 mg/kg/hour i.v. over 72 hours were administered to >500 patients and were well tolerated. For additional information of i.v. administration of anakinra, see Section 5.4.4.1.

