### 6.3.3 Analysis related to primary objective

#### *6.3.3.1 Primary endpoint*

##### Treatment success

The main outcome variable is the percentage of patients requiring mechanical ventilation at 15 days after the start of treatment. The comparison of these proportions would be done by chi-square test, with significance level 0.05 and presentation in the form of absolute risk

reduction, relative risk reduction and number needed to treat, with their respective 95% confidence intervals.

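### Section 6.1 states 75% power for 88% vs 92% success with 90 patients per arm; the planned test has about 13–15%, and the 88% is not explained

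*Protocol*

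**What the plan says.** Protocol section 6.1 gives all the inputs of a two-proportion calculation.

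- **Error rate, power and effect:** at type I error 0.05, "a power of 75% for each comparison under the assumption that the true success rates are 88% in the SoC group increasing to 92" per cent on anakinra.
- **Size:** "It is needed 180 patients (90 per arm) considering a loss of 10" per cent.
- **Basis:** a hospital database of 188 patients, from which "it is estimated that 15% of severe pneumonia COVID patients have required mechanical ventilation".

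Section 3.1.1 defines treatment success as not needing mechanical ventilation by Day 15, so the success rate is one minus the ventilation rate. Section 6.3.3.1 fixes the primary test: "The comparison of these proportions would be done by chi-square test, with significance level 0.05".

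Section 2.3, on what the trial can deliver, says: "Negative results would constitute very useful scientific evidence for abandoning unfounded empirical approaches".

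**The concern.** A difference of 4 percentage points between two success rates near 90% is small, and 90 patients per arm is few. At these rates only about 16 to 18 ventilation events are expected in the whole trial (0.12 + 0.08 = 0.20 events per pair of patients, times 81 or 90 pairs). A power of 75% is not credible on that number of events.

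The control rate raises a second, smaller question. The section says the calculation rests on a 15% ventilation rate, yet it uses 88% success, which is 12% ventilated, and gives no reason.

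An ethics committee or regulator who reads 75% will believe that the trial would probably detect the effect it assumes. If the true power is near 14%, the trial would miss that effect about six times in seven, and a non-significant result would say little about whether it exists. That bears directly on the value section 2.3 places on negative results.

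**Working it through.** **Inputs.** Success rates p1 = 0.88 and p2 = 0.92, alpha 0.05, 90 per arm, 10% loss (section 6.1); chi-square test (section 6.3.3.1). Evaluable per arm: 90 × 0.9 = 81. Sidedness is not stated. The chi-square test is two-sided by construction, so that is the main case, with one-sided as a variant.

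**Step 1: try to reproduce the stated 75%.** With the pooled-variance normal approximation,

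power = Φ{ [ |p2 − p1| − z·√(2·p̄·(1 − p̄)/n) ] / √[ (p1(1 − p1) + p2(1 − p2))/n ] },

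where p̄ = 0.90, 2·p̄·(1 − p̄) = 0.18 and p1(1 − p1) + p2(1 − p2) = 0.1056 + 0.0736 = 0.1792.

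- n = 90, z = 1.96: (0.04 − 1.96 × 0.04472)/0.04462 = −1.068, power 14.3%.
- n = 81, z = 1.96: (0.04 − 1.96 × 0.04714)/0.04704 = −1.114, power 13.3%.
- One-sided (z = 1.645): 22.6% at n = 90 and 21.2% at n = 81.

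Exact enumeration of the uncorrected chi-square test gives 14.5% (n = 90) and 13.2% (n = 81) two-sided, and 22.8% and 21.4% one-sided. With a continuity correction the two-sided figures fall to 8.8% and 7.5%.

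Other variants also fail. At n = 90, unpooled variance and the arcsine method both give 14.4%. Reading 180 as the number per arm gives 24.3% two-sided and 35.2% one-sided. Alpha 0.20 gives at most 52.1% (one-sided, n = 90). The stated 75% is not reproduced.

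**Step 2: size needed for 75% power.**

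n = [1.96·√0.18 + 0.6745·√0.1792]² / 0.04² = (0.8316 + 0.2855)² / 0.0016 ≈ 780 evaluable per arm.

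Allowing for 10% loss, 780/0.9 ≈ 867 per arm, or 1,734 in total. One-sided, it is 605 evaluable per arm (673 with loss).

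**Step 3: use the database rate for control.** Success is 1 − 0.15 = 0.85.

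| Comparison, two-sided 0.05 | 81 per arm | 90 per arm |
|---|---|---|
| 88% vs 92% | 13.3% | 14.3% |
| 85% vs 92% | 28.5% | 31.2% |
| 85% vs 89% (same 4 points) | 11.4% | 12.2% |

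A one-sided test of 85% vs 92% gives 40.1% and 43.1%. Changing the control rate therefore does not rescue the claim.

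**Step 4: what this size can detect with 75% power (two-sided).** From 88%, the anakinra rate must reach about 98.0% (n = 90) or 98.4% (n = 81). From 85%, it must reach about 96.4% or 96.8%.

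**Step 5: precision.** The half-width of the 95% confidence interval for the risk difference at 88% vs 92% is 1.96 × 0.04704 = 9.2 points (n = 81) or 1.96 × 0.04462 = 8.7 points (n = 90). That is about ±9 points around a planned difference of 4.

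**The case against.** The arithmetic is hard to dispute. The objections concern how much can be read into it.

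- **Which number is wrong?** A reader might infer that the power is the faulty entry and that 92% was certainly intended. The protocol does not show this. A pair such as 88% vs 98% gives 90 per arm at 75% power (two-sided, before any loss), so a mistyped rate is possible, though unproven. This stands: the remedy is to recover the inputs and reconcile them.
- **Does 88% contradict the 15%?** It is tempting to say so and to impose 85%. But the 15% describes severe COVID pneumonia patients in one hospital's database. The trial excludes patients already needing intubation, those over 80 and those with life-threatening comorbidity, and it judges success by Day 15. A planned 12% could be a deliberate adjustment. What stands is that no reason is given.
- **Section 2.3 and regulatory use.** The sentence in section 2.3 is general and does not say that anakinra would be abandoned after a non-significant result. Nor does the protocol offer a non-significant result as support for approval: section 6.1 ties regulatory use to a statistically convincing outcome. Neither stronger reading should be made.
- **Signal-finding and added patients.** Section 6.1 speaks of identifying a signal and allows patients to be added if efficacy needs confirming. Both bear on the choice of design, but neither makes 75% true for 180 patients.
- **Two stages.** The powers above ignore the interim look in section 6.3.6. With overall type I error held at 5%, an interim look at the same total size cannot lift power from about 14% to 75%.

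**Conclusion.** The point holds. As written, "a power of 75% for each comparison" is incompatible with the rates, error level and sample size in the same section. The power is about 13–15% two-sided and 21–23% one-sided, and the evaluable sample is more than nine-fold short of what 75% would need (780/81 ≈ 9.6). The unexplained 88% is a secondary fault, since 85% vs 92% still gives only about 28–31%.

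These figures assume equal arms, 81 to 90 evaluable patients per arm, the chi-square test of section 6.3.3.1 without continuity correction, and no cost for the interim look. They do not establish which of the stated inputs is the mistaken one.

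The practical consequence is limited but important. With an interval of about ±9 points, a non-significant result would often be unable to exclude the 4-point benefit the trial assumes, so it is not in itself evidence of no effect.

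**What to change.** Keep 180 patients and correct the text.

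1. Retrieve the inputs entered in the sample-size calculator, and restate section 6.1 so that rates, sidedness, power and sample size agree.
2. Give a reason for 88% success on standard of care, or use the 85% implied by the database.
3. State either the true power for the assumed effect (about 13–15% for 88% vs 92%; about 28–31% for 85% vs 92%) or the difference detectable with 75% power (about 88% to 98%, or 85% to 96.5–97%).
4. Add that a non-significant result will be interpreted through the 95% confidence interval for the absolute risk reduction, expected to be about ±9 points, and is not by itself evidence of no effect. Qualify the section 2.3 sentence on negative results to match.

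The cost is protocol wording only: no extra patients and no change to the primary analysis. The stated power will look much less favourable. Whether to go ahead at that power, or to use the existing provision for adding patients, is then an informed decision for the sponsor.
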